## Study endpoints

### Primary endpoint

The primary endpoint of this study is the incidence rate of MACCEs within one year after patient discharge from the hospital.

MACCEs encompass the following events:
(1)All-cause mortality(2)Cardiac-related mortality(3)Nonfatal myocardial infarction(4)Nonfatal stroke(5)Repeated revascularization procedures

### Secondary endpoints

(1)Incidence rate of all-cause mortality;(2)Incidence rate of cardiac-related mortality;(3)Incidence rate of nonfatal myocardial infarction;(4)Incidence rate of nonfatal stroke;(5)Incidence rate of repeat revascularization procedures;(6)Cardiac function indicators, including LVEF, LVESD, LVEDD, 6-minute walk test (6MWT), and brain natriuretic peptide (BNP) levels;(7)Quality of life scores;(8)Mental health scores, including anxiety scores and depression scores;(9)Biochemical indicators.

### Medications

All of the enrolled patients will receive dual antiplatelet therapy for at least 12 months, according to local practices and current guidelines. Patients will be instructed to take a loading dose of aspirin (300 mg) and either clopidogrel (600 mg) or ticagrelor (180 mg) at least 6 h prior to PCI. Heparin or other antithrombotic agents, such as bivalirudin, are used during PCI. After PCI, long-term treatment with 100 mg of aspirin per day is recommended. Treatment with 75 mg clopidogrel daily (or 90 mg ticagrelor twice daily) should be continued for at least 12 months.

### Digital platform (“Jiuyi” Health App)

The digital health management platform employed in this study was implemented through a smartphone application named JiuYi Health App. Patients could register and access the platform by scanning a designated QR code. Data are encrypted and stored on HIPAA-compliant servers.

The app comprises five core functional modules: Health Data Entry, Physician-Patient Communication, Health Guidance, Alert System, and Health Education. Key features are detailed in the Table 1.

**Table 1 T1:** Key features of the digital platform.

Module	Functional Specifications
Health Data Entry	- Patients upload daily health metrics (e.g., blood pressure, glucose levels, medication adherence, exercise duration, dietary patterns, sleep quality, weight, smoking status, blood oxygen saturation, and psychological status) for physician review. - Automated reminders prompt patients to complete missing entries.
Physician-Patient Communication	- Enables virtual consultations and real-time messaging. - Physicians proactively inquire about health status to enhance treatment adherence.
Alert System	- Triggers automated alerts to patients and physicians upon detecting abnormal values. - Sends reminders for scheduled follow-ups.
Health Guidance	- Physicians analyze uploaded data to generate personalized behavioral recommendations. - Identifies and rectifies incomplete data submissions.
Health Education	- Provides disease-specific multimedia educational resources (text, images, videos) to improve health literacy.

### Follow-up

The enrolling centre will conduct clinical follow-ups via either office visits or phone calls at 30 days (±3 days), 3 months (±7 days), 6 months (±7 days), and 12 months (±30 days) to assess outcomes after discharge.

Standard care includes monthly clinic visits for physical exams, medication adjustment, and 6MWT assessments, plus quarterly phone calls to review symptoms and adherence. All patients receive printed guidelines on lifestyle modifications and medications.

### Intervention protocols

#### Control group

Patients received standard post-PCI outpatient care for 12 months, including:
Pre-discharge education on medication adherence, risk factor management, and follow-up schedules.Structured follow-ups at Months 1, 3, 6, 9, and 12 with the Table 2.

**Table 2 T2:** Standard postoperative follow-up.

Measures	Content
Outpatient monitoring	✓ Routine monitoring: blood pressure, blood glucose, blood lipids, liver function, kidney function, brain natriuretic peptide; medication adherence ✓ Electrocardiogram monitoring: myocardial ischemia, arrhythmia ✓ Medium risk and high-risk patients who have the conditions to wear electrocardiogram monitoring devices for electrocardiogram monitoring can wear electrocardiogram detection devices for monitoring according to their situation after discharge. Monitor electrocardiogram at least once a day within one month after discharge, at least twice a week within three months, and at least once a week within six months. After one year, the monitoring frequency can be adjusted according to one’s own symptoms and follow-up status; If there is discomfort such as chest pain, tightness, palpitations, etc., immediately use wearable devices for electrocardiogram monitoring. ✓ Those who do not have the conditions to wear electrocardiogram testing equipment should regularly go to the hospital to receive electrocardiogram or dynamic electrocardiogram monitoring and evaluation.
Non pharmacological measures	✓ Cardiac rehabilitation therapy should be mainly based on reasonable exercise, while paying attention to a reasonable diet, controlling total calories, and reducing intake of saturated fatty acids, trans fatty acids, and cholesterol. ✓ Weight control: Overweight and obese patients lose 5%–10% weight within 6–12 months. Target value: 18.5 ≤ Body mass index ≤ 25 kg/m^2^; Waist circumference should be controlled within 90 cm for males and 85 cm for females. Weight loss can be achieved by reducing energy intake and exercising. ✓ Do not smoke: Strictly quit smoking, including passive smoking. ✓ Limit alcohol consumption: Strictly control alcohol intake (≤20 g/d for males and ≤10 g/d for non-pregnant females), with a recommended daily alcohol intake of <100 grams/week or <15 grams/day. ✓ Diet: A healthy and balanced diet. Suggest increasing the intake of vegetables, fruits, and whole grains. ✓ Psychological adjustment: Provide patients with multiple, patient and procedural education to fully understand their illness and severity, relieve tension, improve follow-up and treatment compliance, and strengthen self-management; It is necessary to identify the psychological problems of patients and provide targeted treatment. ✓ Exercise: Encourage physical activity and recommend 30–60 min of moderate intensity aerobic exercise per day. However, corresponding exercise guidance should also be developed for patients based on the results of myocardial ischemia and heart function assessment before discharge. In principle, all ACS patients during the rehabilitation period should gradually increase their exercise intensity within the range of not inducing myocardial ischemia and heart function tolerance. Regular reevaluation should be conducted through exercise electrocardiogram or cardiopulmonary function measurement, 6 min walking distance, and dynamic electrocardiogram, and exercise intensity adjustment should be guided.
Pharmacological measures	✓ Strictly follow the doctor's advice when taking medication. If there are special requirements for certain medications (such as long-term use, dosage, etc.), explain them clearly to the patient. ✓ Blood lipids: All recent ACS patients (within 1 year of onset) can be classified as a high-risk population for ASCVD. The target value for lipid-lowering therapy is LDL-C < 1.4 mmol/L (55 mg/dl) and a decrease of ≥50% from baseline. ✓ Blood pressure: Control blood pressure to <140/90 mm Hg, and if tolerable, it can be reduced to <130/80 mm Hg. ✓ Blood sugar: General population: HbA1c ≤ 7%, For patients with high risk of hypoglycemia, such as older patients, longer course of diabetes, impaired renal or liver function, it can be relaxed to <7.5% or < 8.0%.
Rehabilitation therapy	ACS patients should actively participate in cardiac rehabilitation therapy.

#### Experimental group intervention

Within one year after discharge, patients in the experimental group will receive digital platform management based on current routine outpatient postoperative follow-up management.

Specific requirements: In addition to completing all the tasks of the control group, patients in the experimental group are also required to upload daily health data through the platform after discharge, including blood pressure, blood sugar, exercise, diet, sleep, medication information, discomfort symptoms, mental health status, smoking, and other data as required. By uploading data, doctors can timely understand the patient's disease situation and provide personalized rehabilitation guidance, enabling patients to regulate their daily behavior outside the hospital and actively participate in the disease rehabilitation process.

The period for patients to use the digital platform is within 12 months after discharge, and patients need to have follow-up visits at 1, 3, 6, 9, and 12 months after discharge.

Doctors will provide guidance and analysis on the health data uploaded by patients every week, and form a health guidance report for feedback to patients. If communication is needed, patients can be directly communicated through the platform's doctor-patient interaction function to guide their condition and recovery. If patients have any questions or doubts and need to consult doctors, they can also directly communicate through the platform.

#### Follow up matters

The time points for patient follow-up in the study were 1, 3, 6, 9, and 12 months after discharge, totaling 5 times. The specific follow-up contents are shown in the Table 3 below.

**Table 3 T3:** The time points and content for patient follow-up in the study.

Follow up frequency	Follow-up time window	Content	Data
The first time	1 month ± 3 days after discharge	Complete blood routine, biochemistry, myocardial enzymes BNP, Electrocardiogram, cardiac ultrasound and other examinations; Complete the assessment of quality of life questionnaire and mental health questionnaire; For patients with multi vessel, complex, and CTO lesions, if there are chest pain symptoms, hospitalization for coronary angiography is required.	Main indicators: The incidence of major adverse cardiovascular and cerebrovascular events (MACCE); Secondary indicators: The incidence rates of various events in MACCE; Cardiac function indicators; Quality of life rating; Psychological health score; Blood and biochemical indicators Safety indicators: bleeding events, etc
The second time	Within 3 months ± 7 days after discharge		
The third time	6 months ± 7 days after discharge		
The 4th time	9 months ± 7 days after discharge		
The 5th time	12 months ± 30 days after discharge		

The period for patients to use the digital platform is within 12 months after discharge, and patients need to have follow-up visits at 1, 3, 6, 9, and 12 months after discharge (Table 4).

**Table 4 T4:** Follow-up schedule.

Timepoint	Assessments
Baseline (Discharge)	Demographics, GRACE score, LVEF(echocardiography), BNP, lipid profile, 6MWT
1 Month (±3 days):	Clinic visit: Medication adherence (pill count), adverse events, 6MWT. Lab tests: BNP, renal function.
3 Months (±7 days)	Clinic visit: LVEF (repeat echocardiography), quality of life (SF-36 questionnaire), mental health (HADS score).
6 Months (±7 days)	Phone call: Symptom assessment, MACCE screening. Lab tests: Lipid profile, HbA1c.
12 Months (±30 days):	Clinic visit: Final LVEF, 6MWT, SF-36, HADS, MACCE adjudication.

Doctors will provide guidance and analysis on the health data uploaded by patients every week, and form a health guidance report for feedback to patients. If communication is needed, patients can be directly communicated through the platform's doctor-patient interaction function to guide their condition and recovery. If patients have any questions or doubts and need to consult doctors, they can also directly communicate through the platform.

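### Tables 3, 4 and 5 disagree on when bleeding is collected, and only the app arm has a daily symptom channel, so bleeding could be captured unequally between arms

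*Protocol article*

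**What the plan says.** Table 3 (Follow up matters) sorts the follow-up data into main, secondary and safety indicators. The safety entry reads "Safety indicators: bleeding events, etc". It stands beside the first of five visits (months 1, 3, 6, 9 and 12), and the cells below are blank. I read it as one merged cell covering all five, since the same cell holds MACCE.

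Bleeding is not named as an outcome anywhere else. The primary endpoint section states: "The primary endpoint of this study is the incidence rate of MACCEs within one year after patient discharge from the hospital". Its five components do not include bleeding. The nine secondary endpoints end with "Mental health scores, including anxiety scores and depression scores;(9)Biochemical indicators". Table 5 gives each MACCE component its own row but has none for bleeding, only a general adverse-event row.

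Three other statements bear on the point:
- Medications: "All of the enrolled patients will receive dual antiplatelet therapy for at least 12 months".
- Table 1, on the app's communication module: "Physicians proactively inquire about health status to enhance treatment adherence".
- Experimental group intervention: "patients in the experimental group are also required to upload daily health data through the platform after discharge". The list of items includes discomfort symptoms. The section adds: "Doctors will provide guidance and analysis on the health data uploaded by patients every week".

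Study design describes the trial as open-label with blinded endpoints. The only adjudication named is for MACCE, at month 12 in Table 4.

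**The concern.** Every patient is on dual antiplatelet therapy throughout the endpoint year. If the app works partly by improving adherence to it, more bleeding is a foreseeable cost. MACCE would count the ischaemic benefit but, of the bleeding, only deaths and any haemorrhagic strokes. The Conclusion looks ahead to national guidelines if the app proves superior, so readers will want a fair bleeding comparison beside MACCE.

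Two features put that comparison at risk. The three schedules do not agree on when bleeding or adverse events are recorded, so centres could follow different ones. The app arm also has an additional route by which a bleed can come to a physician's notice. Analysis cannot later repair data that were gathered differently in the two arms.

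**Working it through.** **Step 1. The schedules side by side.**

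| Place | What is recorded | When |
|---|---|---|
| Table 3 | Bleeding, as safety indicator | Months 1, 3, 6, 9, 12 (five) |
| Table 4 | Adverse events | Month 1 only; month 6 is a call for symptoms and MACCE screening; month 12 names MACCE adjudication |
| Table 5 | Adverse events, no bleeding row | Days 30, 90, 180, 365 (four) |

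The counts are five, one and four. Month 9 appears in Table 3 but not in Tables 4 or 5.

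**Step 2. The plan's own figure.** Sample size section: p1 = 0.14, p2 = 0.20, mean 0.17.
n = 2 × 0.17 × 0.83 × (1.96 + 0.84)² / 0.06² = 614.6, so 615 per arm as stated. With 10% dropout, 1,230 / 0.9 = 1,366.7, against a stated 1,366. The figure reproduces. It is sized for MACCE alone; the article gives no bleeding rate.

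**Step 3. Effect of unequal capture.** Assumptions, none from the documents: the same true one-year rate r in both arms, and capture fractions s_A (app) and s_C (control). Observed rates are r·s_A and r·s_C, so the apparent risk ratio is s_A / s_C. With n = 615 per arm, the chance of a nominally significant excess at two-sided 0.05 is

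Φ{ [d − 1.96·√(2·p̄·q̄/n)] / √[(p_A·q_A + p_C·q_C)/n] }, where d = p_A − p_C.

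- r = 5%, capture 95% v 80%: 4.75% v 4.00%, about 29 v 25 events. d = 0.0075; (0.0075 − 0.0229)/0.0117 = −1.32; Φ = 0.09.
- r = 5%, capture 95% v 60%: 4.75% v 3.00%, about 29 v 18 events. d = 0.0175; (0.0175 − 0.0216)/0.0110 = −0.37; Φ = 0.36.

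| Capture, app v control | Apparent RR | r = 3% | r = 5% | r = 10% |
|---|---|---|---|---|
| 95% v 80% | 1.19 | 7% | 9% | 15% |
| 95% v 70% | 1.36 | 13% | 20% | 36% |
| 95% v 60% | 1.58 | 23% | 36% | 63% |

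With equal rates and equal capture, the chance of a significant excess in this direction would be about 2.5%.

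**Step 4. Masking.** The apparent risk ratio is the true one times s_A / s_C. A true risk ratio of 0.80/0.95 = 0.84, or 0.60/0.95 = 0.63 at the wider gap, would therefore show as 1.0.

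**Step 5. What equal capture would give.** The 95% half-width for the rate difference is 1.96·√(2p(1 − p)/615): 1.9 points at 3%, 2.4 at 5% and 3.0 at 8%. That is precise enough to be worth reporting.

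**The case against.** The strongest reply is that a usable comparison already exists. Table 3 does not limit bleeding to one arm, both arms attend at months 1, 3, 6, 9 and 12, and Table 5 marks adverse events at common visits for everyone. The Follow-up section also gives standard care monthly clinic visits and quarterly calls about symptoms, which would narrow the contact gap (though the Control group section lists only the five visits). This stands. A reader might infer that the trial can make no valid bleeding comparison, and the documents do not support that.

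The route from upload to record is also inferred. The upload list does not name bleeding, nothing says uploads feed the adverse-event record, and Data collection and management assigns trial data to investigators at each centre. This stands too: unequal capture is a risk, not a stated fact.

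Third, fuller capture in the app arm would exaggerate bleeding there. It would not hide an excess, so the inference that the app could be declared superior while its bleeding cost is concealed by this mechanism fails. The possible distortions are a false excess or a masked reduction.

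Finally, a safety indicator need not be a secondary endpoint, and a grading scale may sit in the full protocol, which is not shown. Neither absence is a finding.

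None of this answers the conflict between the three tables. Nor does the article say that the bleeding comparison will be restricted to what both arms report by the same route.

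**Conclusion.** The point holds in a limited form. The article contradicts itself on when bleeding and adverse events are collected (five, four or one follow-ups), and it leaves open a one-arm reporting channel for the harm most closely tied to the app's intended effect on adherence.

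The possible distortion runs from small to material. At a true 5% in both arms and 615 per arm, the apparent risk ratio is about 1.2 to 1.6, with a 9% to 36% chance of a falsely significant excess. Both the bleeding rate and the capture fractions are assumptions; if the control arm's visits and calls capture nearly as much as the app, the bias is negligible. The five-visit reading of Table 3 rests on treating its blank cells as merged. This should be corrected while recruitment continues, but it does not threaten the MACCE analysis.

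**What to change.** Reconcile Tables 3, 4 and 5 so that bleeding is a named safety outcome with its own row at every follow-up common to both arms, and settle whether month 9 is one of them. At each of those follow-ups, ask the same scripted bleeding question in both arms. Base the between-arm comparison on those reports plus hospital-recorded bleeds, and list bleeds known only from the app separately. The secondary endpoint list can stay as it is.

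The cost is a wording change to the protocol and case report form, plus one question at contacts already planned. The downside is that minor bleeds known only through the app leave the main comparison, though they are still reported. Trial status says recruitment is under way, so patients already followed may lack the scripted question; recording the date of the change lets the analysis take account of it.

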#### Follow up matters

The time points for patient follow-up in the study were 1, 3, 6, 9, and 12 months after discharge, totaling 5 times. The specific follow-up contents are shown in the Table 5 below.

**Table 5 T5:** A timeline for study follow-up.

No.	Category	Item	Specific Indicator	Baseline	Follow-up Periods			
					FU1	FU2	FU3	FU4
					30 ± 3days	90 ± 7days	180 ± 7days	365 ± 30days
1		Informed Consent		×				
2		Inclusion/Exclusion		×				
3		Group Assignment		×				
4	Baseline Data	Demographic Information		×				
		Disease Characteristics		×				
5	Clinical evaluation indicators	MACCE	All-cause mortality		×	×	×	×
			Cardiac mortality		×	×	×	×
			Non-fatal myocardial infarction		×	×	×	×
			Non-fatal stroke		×	×	×	×
			Repeat revascularization		×	×	×	×
		Cardiac Function Parameters	LVEF	×	×	×	×	×
			LVESD	×	×	×	×	×
			LVEDD	×	×	×	×	×
			6MWT	×	×	×	×	×
			BNP	×	×	×	×	×
		Quality of Life		×	×	×	×	×
		Mental Health Assessment	Anxiety score	×	×	×	×	×
			Depression score	×	×	×	×	×
		Biochemical Parameters		×	×	×	×	×
6		Clinical routine examination and evaluation		×	×	×	×	×
7		Deviations			×	×	×	×
8		Adverse Events			×	×	×	×

## Data collection and management

Researchers will receive thorough training on the research requirements to improve data quality and will be involved in the data collection and entry procedures. Data that are required for this clinical trial, such as baseline clinical characteristics, medical treatments, laboratory results, interventional treatments and outcomes, will be collected by investigators at each medical centre. An independent data monitoring committee has been established and will review the accuracy of the data on a quarterly basis.

## Trial status

This clinical trial is still in progress, with participants being recruited from nine medical centres in China. The number of subjects targeted at each medical centre will depend on the daily coronary angiography patient count and the requests from each centre.

## Sample size and statistical analyses

This study will adopt a multicentre, open-label, RCT design, with the primary endpoint being MACCEs at one year after patient discharge. The sample size will be calculated based on this primary endpoint.

The following sample size calculation formula was used:$$n=\frac{2\bar{p}\bar{q}{\left(Z_{\alpha }+Z_{\beta }\right)}^{2}}{{\left(p1-p2\right)}^{2}}$$where “*n*” represents the sample size per group, and Z*α* and Z*β* are obtained from statistical tables. When *α* = 0.05, Z_0.05_ = 1.96. For a power (test efficacy) of 0.9, Z*β* = 1.28; for a power of 0.8, *β* = 0.2, and Z*β* = 0.84. In this study, *α* = 0.05 and *β* = 0.2 were chosen; thus, Z*α* and Z*β* are 1.96 and 0.84, respectively.

“p^−^” represents the mean of p1 and p2, whereas “q^−^” represents the mean of 1-p1 and 1-p2. Additionally, p1 and p2 are the event rates for the experimental and control groups, respectively. Based on previous research (18) and clinical considerations, the one-year MACCE rate for the control group was set at 20% (p2 = 20%). After intervention, the MACCE rate in the experimental group is expected to be reduced by 30%, thus resulting in p1 = 14%.

Using these values in the formula, the required sample size per group (n) is calculated as 615, thus yielding a total sample size of 1,230. With a potential 10% dropout rate considered, the necessary total sample size for this study is 1,366, with 683 patients being allocated per group.

### Statistical analysis

This study will use two-sided tests for the statistical analysis, with a significance threshold set at *α* = 0.05. A *p* value less than 0.05 will be regarded as being statistically significant. The principles for data description and hypothesis testing are as follows:
(1)Statistical descriptionAn analysis will be conducted on the continuous variables to ascertain if they exhibit a normal distribution. Continuous variables that follow a normal distribution will be presented as the means with standard deviations, whereas those that do not follow a normal distribution will be shown as medians with interquartile ranges.

Categorical variables will be presented as frequencies (number of cases) and percentages.
(2)Statistical inferenceFor comparisons between the groups, normally distributed continuous variables will be analysed via independent sample *t* tests. For nonnormally distributed continuous variables, comparisons will be performed via the Mann–Whitney *U* test. Within-group comparisons involving continuous variables with a normal distribution will utilize paired *t* tests, whereas those with nonnormal distributions will employ Wilcoxon rank-sum tests.

*Χ*^2^ tests, Fisher's exact tests, or nonparametric rank-sum tests will be used to compare the categorical variables.

Further analyses will include multivariate model adjustments to account for potential confounding factors and to determine the stability of the results. For comparisons of data at different time points, repeated-measures ANOVA will be used to assess between-group differences over time. Kaplan–Meier curves will be plotted to illustrate the cumulative occurrence of cardiovascular events over time, and log-rank tests will be used for comparisons. Additionally, baseline characteristics will be compared between participants who are included and not included in the final analysis to verify if the missing data are random. Cox proportional hazards models will be used to estimate the hazard ratio (HR) and 95% confidence interval (CI) for the primary endpoint.

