
When considering the somewhat restricted number of clinical studies focusing on the success of internet- and smartphone-based outpatient rehabilitation management for post-PCI ACS patients, as well as the lack of large-sample, multicentre RCTs, the case sources are somewhat restricted, and the generalizability of the research findings is weak.

Therefore, the aim of this study is to conduct a multicentre RCT in China. Additionally, previous clinical assessments have primarily focused on patients' cardiac function indicators, whereby they often used the 6-minute walk distance as the main outcome measure, with limited research on clinical endpoint indicators such as major adverse cardiovascular and cerebrovascular events (MACCEs), patients' quality of life, mental health, and other cardiac function indicators (such as brain natriuretic peptide). Therefore, in this study, in addition to focusing on the 6-minute walk distance as a cardiac function indicator, we will also assess MACCEs, quality of life, and other cardiac function evaluation indicators within and between groups to better understand the impacts of digital health management on the outpatient rehabilitation effect for ACS patients who undergo PCI. These findings will provide a basis for an accessible, affordable, and scalable CR/SP model and provide the foundation for improvements in home-based rehabilitation management.

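### The rank-sum test named for non-normal before-after comparisons is an independent-samples test; the paired signed-rank test should be named instead (minor)

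*Protocol article*

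**What the plan says.** The Statistical analysis section, under statistical inference, sets out tests for continuous variables by type of comparison and by distribution.

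- Between groups, non-normal: "For nonnormally distributed continuous variables, comparisons will be performed via the Mann–Whitney *U* test".
- Within groups, normal: "Within-group comparisons involving continuous variables with a normal distribution will utilize paired *t* tests".
- Within groups, non-normal: "whereas those with nonnormal distributions will employ Wilcoxon rank-sum tests".

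All tests are two-sided at 0.05. The signed-rank test is named nowhere in the article.

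Within-group comparisons are intended. The Introduction says that endpoints will be assessed "within and between groups to better understand the impacts of digital health management". The continuous secondary endpoints include "Cardiac function indicators, including LVEF, LVESD, LVEDD, 6-minute walk test (6MWT), and brain natriuretic peptide (BNP) levels", along with quality of life, anxiety and depression scores and biochemistry. Table 5 schedules all of these in the same patients at baseline and at each of four follow-ups.

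**The concern.** A before-after comparison within one arm uses two values from each patient, so the data are paired. The plan recognises this in the normal case by choosing a paired t test. In the non-normal case it names a test that treats the two time points as two unrelated groups of patients, the same test it gives to the comparison between arms.

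The rank-sum test takes its standard error from independent samples. When a patient's two values are positively correlated, the true variability of the before-after difference is smaller than the test assumes. The p-value is then too large, and some of the power that pairing should provide is lost. BNP and the anxiety and depression scores may well be skewed, so this branch of the plan could be used.

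**Working it through.** **Inputs from the protocol article.** Two-sided alpha 0.05 (Statistical analysis). Event rates 14% and 20%, with Z values 1.96 and 0.84 (Sample size and statistical analyses). Repeated measurement of the same patients (Table 5).

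**Assumptions, not in the documents.** Before-after correlation ρ of 0.3, 0.5 and 0.7. True shift of 0.10 or 0.20 SD (on the log scale for the skewed data). The number of pairs in one arm is taken as the plan's evaluable 615.

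**Step 1: the plan's own figure.** n = 2 × 0.17 × 0.83 × (1.96 + 0.84)² / 0.06² = 0.2822 × 7.84 / 0.0036 = 614.6, rounded up to 615 per group. This reproduces, and it does not depend on the test in question.

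**Step 2: rejection rate when nothing has changed.** With pairs correlated at ρ, the rank-sum z statistic has standard deviation of about √(1−ρ) instead of 1. The actual two-sided rate is about 2 × P(Z > 1.96/√(1−ρ)).

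- ρ = 0.3: 1.96/0.837 = 2.34, rate about 0.019
- ρ = 0.5: 1.96/0.707 = 2.77, rate about 0.006
- ρ = 0.7: 1.96/0.548 = 3.58, rate about 0.0003

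Simulation with 615 log-normal pairs and 4,000 runs per cell gave 0.025, 0.009 and 0.0005 for the rank-sum test, and 0.046 to 0.055 for the signed-rank test on log differences. At ρ = 0 the rank-sum test held its level (0.045). A bivariate normal simulation with 3,000 runs gave 0.007 at ρ = 0.5 and 0.001 at ρ = 0.7. The rank-sum test is unchanged by taking logs, so the two simulations agree apart from chance.

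**Step 3: power (simulated).**

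| ρ | Rank-sum, 0.10 SD | Signed-rank, 0.10 SD, log differences | Signed-rank, 0.10 SD, raw skewed data | Rank-sum, 0.20 SD | Signed-rank, 0.20 SD |
|---|---|---|---|---|---|
| 0.3 | 0.39 | 0.54 | 0.49 | 0.97 | 0.99 |
| 0.5 | 0.37 | 0.69 | 0.62 | 0.98 | 1.00 |
| 0.7 | 0.33 | 0.88 | 0.82 | 0.995 | 1.00 |

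The 0.20 SD columns come from bivariate normal pairs with 2,000 runs per cell. At 0.30 SD both tests are essentially at 1.00.

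**Step 4: why the loss is confined to small shifts.** The standard error that the independent-samples test assumes is about √(2/615) = 0.057 SD, so its threshold is about 1.96 × 0.057 = 0.11 SD. A true shift below this seldom crosses the threshold, and correlation makes that rarer still. A shift well above it crosses nearly always. The choice of test therefore matters for shifts near or below 0.11 SD and hardly at all from 0.20 SD upward.

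**The case against.** The strongest reply is that this is a slip of naming. The sentence sets the Wilcoxon test beside the paired t test, and the sentence before it has already given the independent-samples case to Mann–Whitney. A different name for the within-group test suggests that the other Wilcoxon test was meant. That is plausible, but the text as published names the wrong test, and a programmer who follows it would run it. The repeated-measures ANOVA does not repair this, because the plan assigns it to differences between groups over time. Nor is it a detail left to an analysis plan: the article chose a test and named it.

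The reply also says that little depends on it. That stands. The study hypothesis is between arms, the primary endpoint is MACCE, and positive correlation makes the test conservative, so it does not create false claims of improvement.

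Three stronger readings are tempting, and the documents do not support them.

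- A reader might infer that every non-normal before-after p-value will be wrong. That requires literal execution and a non-zero correlation for every variable. The second condition is usual for repeated measures, but the documents give no correlation.
- A reader might infer that real changes in skewed measures such as BNP would be missed. This is true only for very small shifts, and nothing in the article suggests that change after PCI is that small.
- A reader might infer that within-arm change is to serve as proof of the app's effect. The Introduction refers to comparisons both within and between groups. It does not propose drawing the app's effect from within-arm change alone, or from significance in one arm and not in the other.

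**Conclusion.** The point holds as a minor error in a stated rule: a test for independent samples is assigned to paired data. If the text is followed literally and repeated values are positively correlated, the affected p-values are too large. The actual level is about 2% at a correlation of 0.3 and about 0.1% or less at 0.7, against a nominal 5%. The loss of power is material near 0.10 SD and negligible from 0.20 SD upward. These sizes rest on the assumed correlations and shifts and on 615 pairs per arm. The scope is limited to within-group comparisons of non-normal continuous secondary measures, and no conclusion about the primary endpoint or the difference between arms changes.

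**What to change.** In the within-group sentence of the Statistical analysis section, name the Wilcoxon signed-rank test in place of the rank-sum test, and carry the same wording into any analysis plan. Leave Mann–Whitney for the between-group comparisons. The cost is one word, with no effect on sample size, data collection or the primary analysis. The Trial status section reports that recruitment is still under way, so the wording can be corrected before the final analysis.
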